## Abstract

Suicide is a major public health concern, which disproportionally affects young people. Therefore, effective prevention strategies are needed, but there is a dearth of controlled trials on this topic. Our study will evaluate the effectiveness of a suicide prevention program in Switzerland, where data are scarce. It will test whether the prevention program (1) increases knowledge of suicide and awareness of suicidal risks, (2) provides resources to seek/offer help, (3) increases communication skills related to suicide, (4) increases coping skills, (5) is acceptable, and (6) reduces suicidal ideation and psychological distress. The project will be a single-center cluster non-randomized controlled trial designed to compare an intervention group benefitting from the suicide prevention program with a control group. The potential benefits include a better understanding and evaluation of suicide prevention programs, which may lead to improved primary and secondary prevention practices.

## 1. Introduction

Suicide is the second leading cause of death among young people aged 15 to 29 worldwide [1]. In this age group, the suicide rate is, per 100,000, 10.4 globally, 12.2 in Europe, and 8.5 in Switzerland, respectively. In Switzerland, suicide is the first cause of death among young people (28% of all deaths are attributable to suicide) [2]. Therefore, it constitutes a major public health issue and there is a crucial need for effective prevention strategies. Development of evidence-based suicide prevention programs should be a health policy priority. Reducing adolescent suicide is challenging because young people with suicide ideation rarely seek help [3]. Besides, few programs are evidence-based, so empirical studies with a sound methodology are needed to provide further indication of the effectiveness of the existing preventive programs [4,5]. The paucity of controlled trials designed to evaluate preventive intervention programs has recently been pointed out [6,7,8].

Despite the lack of reliable empirical studies evaluating them, several suicide prevention strategies have been developed at both societal and individual levels. They aim to reduce access to lethal means of suicide, to modify how media report suicide, to reduce psychiatric risk factors (e.g., promoting mental health and targeting at-risk groups) and to promote psychosocial interventions (e.g., reducing discrimination and isolation, promoting social support) [9]. One efficient prevention program is universal school-based interventions, such as the Youth Aware of Mental Health Program [10]. This kind of program usually uses interactive workshops including lectures about mental health and suicide, role-play sessions, and paper supports (e.g., booklets). Such programs are designed to raise awareness of suicide and risk factors to dispel myths about suicide, promote help-seeking behaviors, and develop adolescent coping skills. They are more effective than other school-based interventions to reduce suicide attempts and severe suicidal ideation [11]. Most published studies relied on school-based programs because they constitute the most effective way to reach young people. However, these interventions miss young people who are no longer enrolled in school, which is likely for those who are transitioning to adulthood. Therefore, none of the previous studies evaluated the full spectrum of possible interventions to prevent suicide among young people [7].

Prevention programs should be culturally sound. Indeed, attitudes toward suicide can vary widely between countries and regions and the way in which each community considers and experiences suicide should be taken into account. To our knowledge, no evaluation of suicide programs in school and community settings have been published in Switzerland. Even if there have been cantonal suicide prevention programs, the first Swiss national program on suicide prevention was created in 2016 [12]. In the French-speaking part of Switzerland, *Stop Suicide* delivers workshops for suicide prevention. The main aim of the workshops is to raise awareness of suicide and to provide resources to seek and offer help. More specifically, the covered topics include general information on suicidal behavior, ways to identify the risk factors and warning signals of suicide, myths and facts about suicide, how to ask questions, how to seek help, and how to provide support. The workshop has a duration of 90 min. The program includes one lecture, case examples with a group discussion, creation of a poster based on the group discussion, and an illustrated book. The facilitators include a staff member of *Stop Suicide*, who is trained to deliver it and to detect/manage suicidal risk, and a psychologist trained for suicide prevention and evaluation of suicidal risk, available during and after the workshop. It targets young people (males and females) aged between 14 and 29 in several different settings (e.g., schools, vocational schools, universities, and other higher education institutions, and settings for unemployed and disabled youths). *Stop Suicide* conducts an average of ten workshops per months (~1800 young people per year).

Therefore, this study will provide new insights into the effectiveness of this suicide prevention program in Switzerland, promoted by the association Stop Suicide (https://stopsuicide.ch). The project will test the following hypotheses:

**Hypothesis 1** **(H1).**The program increases knowledge of suicide and awareness of suicidal risks, including risk and protective factors.

**Hypothesis 2** **(H2).**The program provides resources to seek/offer help (e.g., whom young people can contact to seek help).

**Hypothesis 3** **(H3).**The program increases communication skills related to suicide (e.g., willingness and confidence to talk about suicide).

**Hypothesis 4** **(H4).**The program increases coping skills and young people are more able to manage stress related to adverse life events.

**Hypothesis 5** **(H5).**The program is acceptable (i.e., enjoyable and worthwhile for participants).

**Hypothesis 6** **(H6).**The program reduces suicide-related behaviors (suicidal ideation) and psychological distress.

## 2. Materials and Methods

### 2.1. Design

This study is a single-center cluster non-randomized controlled trial designed to compare an intervention group benefiting from the suicide prevention program with a control group. The study includes follow-ups at one and three months after the baseline assessment.

### 2.2. Participants

The study will take place in different settings in the French-speaking part of Switzerland. Workshops will take place in schools (classes) and community settings (associations, vocational schools, and homes/residential centers). We will recruit clusters from these settings. All young people are eligible to participate in the study with the following exclusion criteria: (1) Being under 14 years of age and (2) not being able to communicate in French.

### 2.3. Procedures

We will propose the study to all schools and community settings in which *Stop Suicide* delivers suicide prevention programs. We plan to rely on a random assignment to the intervention group or the control group. Participants from the control group will participate in the workshop at the end of the project. However, the final design cannot be considered as a pure randomized controlled trial since some schools or community settings may refuse to participate in the study before the workshop.

The first visit will start with the explanation of the study. Then, young people who consent to participate will complete the self-reported questionnaire (baseline assessment) (max. 20 min). 

For the intervention group, the suicide prevention program will be delivered right after to all young people, including those who did not consent to participate in the study. This one-and-a-half-hour universal program will be given in classes (or community settings) by the staff of *Stop Suicide*, who is trained to deliver it. For the control group, the first visit stops after the completion of the self-reported questionnaire.

The second visit will take place one month after the intervention (first follow-up). It will include the same questionnaires (excepted socio-demographic variables) as in the baseline assessment (max. 20 min).

The third visit will occur three months after the intervention (second follow-up). It will include the same questionnaires as in the first follow-up (max. 20 min). The control group will be delivered the workshop after the third visit.

Dissemination of information to different settings started in May 2019. Data collection will start in June 2019 and is planned to end in June 2020.

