#### 2.5.2. Data Analysis

The project will use an intention-to-treat analysis. For all analyses, we will use three-level mixed-effect models, with measures nested in participants, who are themselves nested in classes/community settings. To provide a better overview of the benefits of the program, we will also use a per-protocol analysis. For all statistical analyses, we will use a two-sided α = 0.05. We will use a Bonferroni–Holm adjustment for multiple testing. When possible, the measures of effect size will be used to provide an estimation of the clinical significance of the findings. Statistical software will include Stata 15, SPSS 25, and R 3.4.3.

*Preliminary analyses:* We will examine the variables for distributional properties, correlations, and patterns of dropouts and missing data. We will compute descriptive statistics for each item and also for each scale. We will also check the reliability of the scales, especially for those that have not been described in previous studies. We will test differences between the intervention and the control group at baseline (socio-demographics and outcome variables) to confirm that the groups are comparable, especially if we cannot achieve a randomized allocation.

*H1. Increase in suicide knowledge and awareness of suicidal risks:* We will compare the mean scores of the literacy of suicide scale and the knowledge of what to do in case of suicidal thinking between the intervention and control groups.

*H2. Increase in skills related to how to seek/offer help:* We will compare the mean scores of help-seeking between the intervention and control groups.

*H2. Social networks:* Social networks of peers will be analyzed using exponential random graph models. Social networks of people outside the class are personal networks, rather than closed networks, so it will not be possible to use exponential random graph models. We will derive different variables (family support, friends’ support, other) to see whether there is an increase over time. We will explore different research questions: Is the density of social support related to suicidal thoughts and psychological distress? Is the diversity of social support related to a reduced level of suicidal thoughts and psychological distress? Does the program increase the density of social support?

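### Individual consent and baseline appear to follow the cluster's allocation, with no step that withholds the arm, so enrolment and baseline answers may depend on it

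*Protocol article*

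**What the plan says.** All references are to the protocol article.

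- **Unit of recruitment and assignment.** Section 2.1 describes a cluster, non-randomized controlled trial. Section 2.2 says "We will recruit clusters from these settings", and section 2.3 adds "We plan to rely on a random assignment to the intervention group or the control group".
- **The caveat given.** The reason offered in 2.3 for not calling the trial a pure randomized one is that "some schools or community settings may refuse to participate in the study before the workshop". That concerns settings. Consent by individuals within a participating cluster is not mentioned as a threat.
- **The first visit (2.3).** It opens with the explanation of the study. "Then, young people who consent to participate will complete the self-reported questionnaire (baseline assessment) (max. 20 min".
- **What follows in the intervention group (2.3).** Here "the suicide prevention program will be delivered right after to all young people, including those who did not consent to participate in the study".
- **What follows in the control group (2.3).** "For the control group, the first visit stops after the completion of the self-reported questionnaire". Controls receive the workshop after the third visit.
- **Analysis (2.5.2).** "The project will use an intention-to-treat analysis". Baseline differences between the groups will be tested. Follow-up scores will be modelled on group and the baseline value of the outcome, with control for socio-demographic variables and other potential confounders assessed in the study.

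**The concern.** Random assignment of clusters balances the clusters. It balances the enrolled individuals only if joining does not depend on the arm. When people are recruited after their cluster has been allocated, and they or those presenting the study know the allocation, the consenters in the two arms can be different kinds of people. This route to bias is separate from refusal by settings, and it stays open even if every setting accepts its assignment.

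Selective consent is plausible here. The questionnaire (2.4) asks about suicidal thoughts, psychological distress and willingness to talk about suicide, and it asks for classmates' full names. Readiness to answer such questions may be related to the outcomes of H3 and H6. For H2, a difference in consent between arms could also make the class networks less complete in one arm than in the other.

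The baseline may be affected too. It is self-reported, and a young person who expects a suicide-prevention workshop within minutes may answer differently from one who does not. The planned adjustment relies on that measurement.

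**Working it through.** **1. Is the arm set before consent?** The article does not state the order, so it has to be inferred from 2.3.
- The workshop in intervention clusters starts directly after the questionnaire and is given by trained staff, so it must have been arranged beforehand.
- In control clusters nothing follows the questionnaire.
- A visit that continues in one arm and ends in the other can hardly be run unless the arm is known to the study team in advance. Individual consent and baseline therefore very probably come after allocation.

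**2. Does any described step close the route?**
- *Concealment:* 2.3 describes none.
- *Intention-to-treat:* it keeps enrolled people in their assigned arm. Non-consenters supply no data.
- *Baseline tests:* they compare consenters with consenters.
- *Adjustment:* it covers measured variables, and one of them is the baseline collected in this same visit.

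**3. The plan's own figure.** Inputs from 2.5.1: difference 1, variance 6, two-sided 5%, power 80%.
- n per group = 2 × 6 × (1.960 + 0.842)² / 1² = 94.19, rounded up to 95, or 190 in total. The stated figure reproduces.
- The planned 150 per group gives 94.2% power if individuals are treated as independent.
- The present point changes neither number. It concerns bias, not sample size. The variance implies an SD of √6 = 2.45.

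**4. Possible size of selection.** The article gives no consent rates, so the rates and the gap k below are assumptions.
- With consent rate c, and consenters differing from non-consenters by k SD, the consenters' mean differs from the whole-class mean by (1 − c)k.
- With the same k in both arms and no programme effect, the arms differ by [(1 − c₀) − (1 − c₁)]k.

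| Consent, one arm v the other | k | Shift in SD | Shift at SD 2.45 |
|---|---|---|---|
| 90% v 80% | 0.5 | (0.20 − 0.10) × 0.5 = 0.05 | 0.12 |
| 90% v 70% | 0.5 | (0.30 − 0.10) × 0.5 = 0.10 | 0.24 |

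The last column is for scale only, since 2.5.1 does not say which outcome the variance of 6 belongs to.

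**5. Effect on a test.** At 150 per arm, without clustering or adjustment, SE = 2.45 × √(2/150) = 0.283. With no true effect, a shift of 0, 0.1 or 0.25 points gives a false-positive rate of 5.0%, 6.4% or 14.3%.

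**6. After baseline adjustment.** Assume a baseline to follow-up correlation of 0.6.
- If the same shift is present at both times, (1 − 0.6) of it remains: 0.02 to 0.04 SD, or about 0.05 to 0.10 points.
- If instead expectation moves only the baseline answers, adjustment creates an error of the opposite sign. A baseline shift of 0.10 SD would give 0.6 × 0.10 = 0.06 SD.

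**The case against.** The strongest reply is that 2.3 describes explanation, consent and baseline once, in common for both groups, and separates the arms only after the questionnaire. Nothing says that the explanation differs by arm or that young people know their arm when they decide. An article need not print its consent script, and the team may already disclose the arm only after baseline.

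Much of this stands. A reader might infer that willingness to join does differ by arm, or that baseline answers are given in the knowledge of what comes next. The article supports neither; it supports only that both could happen. Nor can the workshop itself contaminate the baseline, because the questionnaire comes first; only knowledge or expectation of the arm could.

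Two further objections also stand in part.
- *Incentive:* access to the workshop does not depend on consent. Intervention non-consenters receive it the same day and controls receive it later. This removes the most obvious reason for consent to differ, and the direction of any bias cannot be predicted.
- *Size:* the figures rest on assumed inputs, are small beside the planned difference of 1, and shrink under adjustment if the baseline carries the same shift. The SD of 2.45 is not tied to the H3 or H6 measures, and suicidal ideation consists of two yes/no items.

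The reply does not remove the point. The article does set out the sequence of the visit and does discuss what threatens its randomization, but that discussion stops at refusal by settings. Withholding the arm is a procedural choice, and analysis cannot supply it afterwards.

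**Conclusion.** The point holds as a possible bias, not a demonstrated one. The visit described in 2.3 implies that the cluster's arm is settled before individuals consent and complete the baseline, and no step keeps the arm from them at that stage. Cluster randomization would not prevent selective enrolment, intention-to-treat does not address it, and adjustment can only partly do so.

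The true size cannot be derived from the article. The illustrative 0.05 to 0.10 SD rests on three assumptions: a 10 to 20 percentage point gap in consent, a 0.5 SD difference between consenters and non-consenters that is equal in both arms, and no adjustment. With equal consent rates and that common difference it is zero. The planned sample size is unaffected. The change is worth making because it is cheap and because selective enrolment cannot be repaired once it has occurred, but this is not a flaw that by itself invalidates the comparison.

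**What to change.** In section 2.3, without changing the order of the visit:

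1. Use one identical explanation and consent script in both arms. It should say that the workshop will be given either that day or after the last follow-up visit, which is the schedule already planned.
2. Collect consent and the completed baseline before the class or group is told its arm and before the workshop is announced.
3. Record the number present and the number consenting in every cluster, and report consent by arm.

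The cost is a shared script and a headcount. The small downside is that setting staff who know the timetable must be asked not to disclose it, and concealment may be imperfect. The consent counts would then let readers see whether enrolment differed between the arms.

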### 2.4. Measures

The whole French questionnaire is available in Supplementary Materials.

*Knowledge and awareness of suicide (H1)*. We will use seven items from the Literacy of Suicide Scale (LOSS) [13] to assess an increase in suicide knowledge and awareness of suicidal risks (five items of the original twelve-item scale are not discussed during the workshop). The items are assessed as true or false, leading to a total score of correct responses between 0 and 7 (Cronbach alpha = 0.77).

*Seek/offer help (H2)*. We will use the six items used in Bailey et al. [14] and a five-point scale to assess knowledge of what to do in case of suicidal risk and how to seek help. We will also use six self-developed items and a five-point scale to assess knowledge of where to seek help in the case of suicidal risk (e.g., “I know where to go for help if I have suicidal thoughts”, “I know a phone number to call for help”).

*Social network (H2)*. In addition, we will ask the participants to answer the two following questions:With which classmates do you feel comfortable speaking about problems?With which person outside the class do you feel comfortable speaking about problems?

For classmates, we will ask for first and last names in order to be able to create the complete class network. For persons outside the class, the participants will be invited to provide a first name and their relationship with this person (e.g., mother, father, sibling, friend, neighbors). We will be able to draw personal networks from this question and disentangle the family network from the peer network.

*Willingness and confidence to talk about suicide (H3)*. We will use the eight items used in Bailey et al. [14] on a five-point scale (Cronbach alphas: Willingness: 0.76, confidence: 0.60).

*Coping skills and management of adverse life events (H4)*. Two subscales from the COPE inventory [15] will be used: Seeking social support for instrumental reasons (Cronbach alpha = 0.75) and seeking social support for emotional reasons (Cronbach alpha = 0.85). Each subscale has four questions assessed on a four-point scale.

*Acceptability (H5)*. Acceptability will be assessed using six questions from Bailey et al. [14] (five-point scale).

*Suicidal ideation (H6)*. We will use two items related to the presence of suicidal ideation of the Columbia-Suicide Severity Rating Scale (C-SSRS, Cronbach alphas between 0.73 and 0.95), including a lifetime and past-month screen of suicidal thoughts (yes/no answers) [16].

*Psychological distress (H6)*. We will use the six items of the Kessler Psychological Distress Scale (K-6) [17,18] to assess psychological distress (five-point scale).

*Sociodemographic variables*. We will assess gender, age, type of school, and parental level of education.

### 2.5. Analytical Strategy

#### 2.5.1. Sample Size Calculation

With a confidence of 95%, a power of 80%, an expected difference between the two groups of 1, and a variance of 6, a sample of *n* = 190 (95 participants in each group) is needed to detect a statistically significant difference. We plan to include *n* = 300 participants (*n* = 150 in each group).

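### The 190 said to be needed for 80% power assumes independent participants in a trial that recruits and models clusters, and the planned 300 carries no stated power

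*Protocol article*

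**What the plan says.** The Sample Size Calculation (section 2.5.1) opens with "With a confidence of 95%, a power of 80%, an expected difference between the two groups of 1, and a variance of 6" and concludes that a total of 190 follows, of which "95 participants in each group) is needed to detect a statistically significant difference". It then states a larger target: "We plan to include *n* = 300 participants (*n* = 150 in each group". No reason and no power are attached to the larger number, and clustering is not mentioned.

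Elsewhere the same article is explicit about clustering:

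- Section 2.1: "This study is a single-center cluster non-randomized controlled trial".
- Section 2.2: the units recruited are clusters drawn from schools and community settings.
- Section 2.3: the workshop is given to everyone present in an intervention class or setting, including those who decline the study.
- Section 2.5.2: the analysis uses "three-level mixed-effect models, with measures nested in participants, who are themselves nested in classes/community settings".

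**The concern.** Design, recruitment, delivery and analysis all treat the class or setting as a unit. The power calculation does not. Two participants from the same class then tell us less than two from different classes, and the variance of the group difference is larger than the formula assumes. The claim that 190 gives 80% power is therefore not a property of this design.

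The practical stake is how 300 is read. Set beside a requirement of 190 it looks like a comfortable margin; under independence 300 would have 94% power. Part of that margin is taken up by clustering, and part may be taken up by loss over the two follow-ups. The article does not say how much remains. A reader weighing a non-significant result needs that figure.

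**Working it through.** **Inputs.**
- Difference 1, variance 6, power 80%: section 2.5.1.
- Significance level: "For all statistical analyses, we will use a two-sided α = 0.05" (section 2.5.2).
- Cluster size m: not stated. The Introduction says that the association "conducts an average of ten workshops per months (~1800 young people per year"). That gives 1800 / (10 x 12) = 15 per workshop. Consenting participants per cluster may be fewer or more, so 10 and 25 are also shown.
- ICC: not given. A range of 0.01 to 0.10 is assumed.

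**Step 1: reproduce the stated figure.** For independent participants,

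n per group = 2 x 6 x (1.960 + 0.842)^2 / 1^2 = 94.19, rounded up to 95, so 190 in total.

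This is an exact match with design effect 1. A one-sided test would give 75 per group and does not match.

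**Step 2: slack in 190.** 95 / 94.19 = 1.009, so 190 tolerates a design effect of at most about 1.009. With design effect DE = 1 + (m - 1) x ICC and m = 15, the limit is ICC = 0.0086 / 14 = 0.0006.

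**Step 3: power with clustering, m = 15, no loss, no baseline adjustment.** Power = Phi(1 / sqrt(2 x 6 x DE / n) - 1.96), with n per group. Example at ICC 0.05, n = 150: DE = 1 + 14 x 0.05 = 1.70; 1 / sqrt(12 x 1.70 / 150) = 2.71; Phi(2.71 - 1.96) = Phi(0.75) = 77%. The t column uses a noncentral t on 18 df, from 150 / 15 = 10 clusters per group and 20 - 2 = 18. The last column is the minimum detectable difference for 300 at 80% power, 2.802 x sqrt(12 x DE / 150).

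| ICC (assumed) | DE | Power, 190 | Power, 300 | Power, 300, t on 18 df | Detectable difference, 300 |
|---|---|---|---|---|---|
| 0.01 | 1.14 | 75% | 91% | 88% | 0.85 |
| 0.02 | 1.28 | 70% | 88% | 84% | 0.90 |
| 0.05 | 1.70 | 58% | 77% | 73% | 1.03 |
| 0.10 | 2.40 | 44% | 63% | 58% | 1.23 |

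**Step 4: ICC at which 300 has exactly 80% (normal approximation).** 150 / 94.19 = 1.59 is the largest design effect that 300 can absorb, so the break-even ICC is 0.5926 / (m - 1):

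- m = 10: 0.5926 / 9 = 0.066
- m = 15: 0.5926 / 14 = 0.042
- m = 25: 0.5926 / 24 = 0.025

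With an assumed 20% loss (120 per group, m = 12), 120 / 94.19 = 1.274 and 0.274 / 11 = 0.025. Using the rounded 95 instead gives (120 / 95 - 1) / 11 = 0.024.

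**Step 5: effect of baseline adjustment.** If a baseline-outcome correlation r reduces variance by the factor 1 - r^2 at both levels (an assumption), 300 reaches 80% at ICC 0.05 and m = 15 when 1.70 x (1 - r^2) = 1.59, that is r = about 0.25.

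**The case against.** The strongest reply is that nobody plans to run a trial of 190. The target is 300, which absorbs a design effect of almost 1.6, and the main analysis already has a class or setting level, so the validity of the test is not in question. This stands. A reader might infer from the mismatch that the trial is underpowered; the document does not support that. It gives no ICC. At small ICCs 300 stays above 80%, by the normal approximation even with a 20% loss up to an ICC of about 0.024.

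Several points also make the power figures softer than a single table suggests:

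- The 1800 young people per year are workshop attendees, not consenting participants. With 10 per cluster, power of 300 at ICC 0.05 is about 84% (DE 1.45); with 25 it is about 66% (DE 2.20).
- Section 2.5.2 plans to adjust for the baseline level of each outcome. With r = 0.5, on the assumption in step 5 of the working, power at m = 15 would be about 88% at ICC 0.05 and 75% at 0.10. Section 2.5.1 neither uses this nor gives a correlation.
- The variance of 6 is taken as stated, although the section does not say which outcome it belongs to.

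The last defence is that an article condenses its protocol, and that an ICC, cluster counts and attrition may be set out there. Their absence alone would indeed be no finding. But condensation cannot rescue the 190: the printed inputs account for it fully at design effect 1, with room for no more than 1.009. The surplus up to 300 may well be meant for clustering or dropout; the text does not say so.

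**Conclusion.** The point holds in a limited form. The arithmetic behind 190 is right for independent participants and does not fit the cluster design described in the same article. On the stated inputs, 190 does not give 80% power for any ICC above about 0.0006 at 15 per cluster.

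Whether 300 is enough is open. Without loss or baseline adjustment it depends on whether the ICC lies below about 0.025 to 0.066, according to cluster size (25 down to 10), by the normal approximation; the cluster-level t reference gives somewhat lower power. These limits rest on an assumed ICC, on a cluster size derived from attendance figures, and on the stated difference and variance. What can be said firmly is that the article's one power statement does not describe its own design, and that the power of the number actually planned is not reported.

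**What to change.** Rewrite section 2.5.1:

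1. Withdraw the statement that 190 gives 80% power, or label it as the figure for independent participants before any allowance for clustering.
2. Report the power, or the minimum detectable difference, of the planned 300 with design effect 1 + (m - 1) x ICC, over a range of m (for example 10 to 25) and ICC (0.01 to 0.10).
3. Give the expected number of clusters per group and use a t reference with cluster-level degrees of freedom.
4. State an attrition assumption for the two follow-ups, and say what the increase from 190 to 300 is meant to cover.
5. If baseline adjustment is counted on, state the baseline-outcome correlation used.

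The cost is one paragraph. No extra participants and no change to the analysis model are needed. The downside is a stated power less favourable than the present text suggests.
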